## Abstract

**Introduction:**

Focused deterrence (FD) is a frequently cited intervention for preventing violence, particularly against violent urban gangs. The Youth Endowment Fund (YEF) believes it could be effective in the UK, based primarily on research conducted in the US. However, we contend that these studies have inadequate methodological designs, lack of rigorous testing, and small sample sizes. Therefore, the evidence supporting focused deterrence as an effective method, particularly outside the US, is inconclusive. The aim of the protocol is to better understand the potential effects of FD in the context of the UK, using a multisite evaluation experimental design to more closely investigate the evidence of its likely impact.

**Methods:**

We planned a realist randomised controlled trial. The design is focused on a multisite trial consisting of two-arm randomised experiments in five locations. Each trial location will test their implementation of a core programme specified by the funder. The multisite nature will allow us to understand differential impacts between locations, improving the external validity of the results. Participants will be randomly selected from a wider pool of eligible individuals for the intervention. We estimate a sample size of approximately *N* = 1,700 individuals is required. Based on this pooled sample size, a relative reduction of 26% would be detectable in 80% of trials. The trial is coupled with a formative process evaluation of delivery and fidelity. The formative evaluation will use a mixed methods design. The qualitative aspect will include semi-structured cross-sectional and longitudinal interviews with programme leads, programme delivery team, and programme participants, as well as observations of the meetings between the programme delivery team (i.e., community navigators/mentors) and programme participants. The quantitative data for the formative evaluation will be gathered by the sites themselves and consist of routine outcome performance monitoring using administrative data. Sampling for interviews and observations will vary, with the researchers aiming for a higher number of individuals included in the first round of cross-sectional interviews and retaining as many as possible for repeat interviews and observations.

**Discussion:**

This protocol outlines the process and impact evaluation methodology for the most extensive multisite evaluation of focused deterrence to date in the UK. Spanning five distinct sites with seven trials, the evaluation includes a cohort of 2,000 individuals, marking it as the only multisite trial of focused deterrence. Employing an integrated realist evaluation framework, the study uses qualitative and quantitative research methods. The anticipated findings will offer pivotal insights for formulating future violence prevention policies in the UK. They are also expected to contribute significantly to the corpus of literature on violence prevention and intervention evaluation.

**Trial registration:**

**Protocol registration**: ISRCTN: 11650008 4^th^ June 2023.

## Introduction

Violence is a leading cause of injury and mortality among young people worldwide [1]. It is associated with physical, psychological [2] and social harms [3] to victims, and potentially harmful contact with the criminal justice system for perpetrators [4, 5]. It also acts as a ‘signal’ of social disorder [6] to the wider population, affecting fear of crime and feelings of safety. Following a steady decline in all types of violence in the early 2000s, rates of police-recorded violence in the UK have trended upwards since 2013/14 [7]. In 2018, the Serious Violence Strategy [8] established “a new balance between prevention and effective law enforcement” (p.7) as the approach of the government of England and Wales to reducing violence, particularly violence involving young people. Since the publication of this strategy, over £800m has been allocated to finding and implementing effective violence prevention in England and Wales, often through the importation of interventions from the US. Although modest progress has been made in reducing violence in some areas [9], robust evidence of what works to reduce community violence in England and Wales remains elusive.

Focused deterrence is one of the most promising interventions for addressing community and youth violence [10, 11]. It has been implemented in dozens of jurisdictions across diverse urban settings, predominantly in the United States, with published evidence generally indicating positive effects in reducing serious violence [12, 13]. Similarities in the likely causes of community violence between the US and the UK mean that focused deterrence has the potential to be effective in the UK. However, past attempts to implement focused deterrence have met with implementation challenges [14] or inconclusive evidence of effectiveness [15, 16], and the importance of contextual differences in violence, policing, support services and community attitudes is not well understood. In particular, the prevalence of homicide and other serious violence in England and Wales—the rate of homicide is six times higher in the US [17]—means that there are likely to be fewer opportunities for intervention and rarer outcomes in England and Wales compared to the US.

Focused deterrence interventions are adapted to their location, but all include some combination of the following principles: (1) The intervention targets individuals and/or groups identified as being involved in serious violence in a community or area. These individuals are identified using intelligence from various official and community sources. They are informed that they are the focus of police attention and that various mechanisms will be activated, such as disruption to their daily activities and withdrawal of or reduction in statutory services, such as housing, should they continue to participate in violence. (2) They are also informed that, should they wish to desist from violence, a variety of support services will be made available to them to facilitate this desistance. (3) To underline the legitimacy and credibility of this message, it is conveyed by a combination of police, statutory and voluntary sector organisations, and community members in different formats. These three components—making violence less attractive through increased perceived probability of consequences, creating additional opportunities to desist from violence, and signalling community support for both components—bring together core theories of crime prevention that may have separate mechanisms but may also interact to affect violence outcomes.

### Aims

The study aims to evaluate the efficacy of focused deterrence as an intervention for reducing violent offending among individuals aged 14 and older who are at risk of violent offending in England. The study uses a multi-site parallel randomised controlled trial (RCT) design to assign participants to an intervention or a control group in a 1:1 ratio, with stratification based on age (adult/child status) and prior offending frequency. This design will facilitate a robust assessment of the intervention’s impact on the occurrence of violent offending within this demographic.

## Methods and materials

### Realist multisite randomised controlled trial

To achieve the aims of the study, we designed it as a realist randomised controlled trial. The design includes a summative impact, multisite two-arm randomised evaluation, a formative process evaluation of both delivery and fidelity of the intervention, and longitudinal qualitative accounts of the intervention experience.

As one of the first such studies to use individuals as treatment groups, no feasibility study, pilot, or effect estimate was available to inform our study design. To overcome this limitation, we conducted power simulations using pre-baseline outcome data for the trial cohort using a range of plausible effect sizes. These simulations indicated that no one city was likely to have sufficient availability of offenders or frequency of outcomes to permit a well-powered trial within the funding period of the project. Accordingly, the study was set up as a multisite trial to achieve a large enough sample size for a robust experimental design of individual-level interventions. The success of this approach depends on consistent intervention delivery and evaluation across all sites. However, achieving such consistency is challenging in complex community settings with multiple partners. The protocol for this evaluation has been preregistered [18] and it notes that manualised interventions are unlikely to be exactly replicated in different violence prevention contexts. Despite receiving comparable resources and guidance, the five sites designed similar, but not identical, interventions based on their local contexts.

Without a feasibility study for a multisite trial, this study includes careful process monitoring to check treatment fidelity across sites and tries to control intervention and evaluation processes as much as possible. Since the evaluation team is not responsible for the programme design or delivery, ongoing observation and assessment are vital to justify pooling study data. The process evaluation will check the consistency of delivery throughout the trial period.

Our divergence from group to individual treatment units represents a trade-off between the feasibility of achieving sufficient statistical power and the theory that a group-level mechanism is essential for a focused deterrence intervention to be effective. In effect, a randomised controlled trial using a group as the treatment unit is not possible within available resources and England and Wales population parameters (the remit of Youth Endowment Fund). The multisite design will let us assess the between-site variability of an intervention that, on paper, has the same core components. Combining this with a realist evaluation, we can then try to disentangle how implementation has varied. This can, however, be challenging for multi-agency interventions developed within complex environments.

### Intervention sites

This multisite trial, spanning five English cities—Coventry, Leicester, Manchester, Nottingham, and Wolverhampton—implements seven distinct interventions, all structured around the YEF Focused Deterrence framework (see Table 1). While each intervention adheres to the same foundational aims and theoretical underpinnings, adaptations have been made to accommodate variations in local contexts, resource availability, and organisational structures. For a comprehensive understanding of each intervention’s unique and common elements, detailed accounts, structured following the TiDieR (Template for Intervention Description and Replication) framework, are available on the Open Science Framework: https://osf.io/pvnj2/.

**Table 1 pone.0301023.t001:** Seven interventions across five sites and four delivery teams.

Trial number	Team	Site	Intervention name
1	Leicester, Leicestershire and Rutland Violence Reduction Network	Leicester City	The Phoenix Programme
2	Greater Manchester Combined Authority	Manchester City	Another Chance Manchester
3	Nottingham Violence Reduction Unit	Nottingham City	Another Way
4	West Midlands Police	Coventry City	CIRV Coventry high risk pathway
5	West Midlands Police	Coventry City	CIRV Coventry referral pathway
6	West Midlands Police	Wolverhampton City	CIRV Wolverhampton high risk pathway
7	West Midlands Police	Wolverhampton City	CIRV Wolverhampton referral pathway

### Eligibility criteria and recruitment

Participants who might be eligible for the intervention are identified through police records and, in exceptional circumstances, may be referred through statutory services. A set of strictly defined eligibility criteria is then used by each site to identify potential participants from this pool. For example, in Nottingham, participants must:

live within the defined boundaries for the site area;have group bonds formed from time spent in the area or have familial ties to the area;have been arrested for violence against a person, robbery, or weapon possession in the 12 months preceding the start of the intervention;have been arrested for one or more of the following offences as part of a group of three or more in the preceding 24 months: violence against the person, criminal damage and arson, robbery, drug offences, possession of weapon offences or public disorder.

Multi-agency programme panels then triage this shortlist of eligible participants at each site. The triaged list is also assessed for deconfliction (i.e., the removal or suspension of anyone subject to active police enforcement for organised crime activity) and the eligible cohort is then randomized into treatment and control groups.

### Statistical power

In the absence of a feasibility or pilot study on which to base estimates of statistical power, we sought to simulate the trial and to deduce a range of required sample sizes based on plausible effect sizes.

#### Data

As part of the preparation phase, the five sites were asked to develop selection/eligibility criteria for the intervention, to identify the number of these individuals in their population, and to describe the number of police-recorded violence against the person offences attributed to them in a twelve-month period. This information allowed us to describe the distribution of outcomes (negative binomial) and to identify the anticipated number of individuals in treatment and control groups.

#### Effect size

As the focused deterrence literature is largely based on population-level treatment effects using quasi-experimental designs and a set of outcomes (e.g. firearm homicide) that are very rare in a UK context, the study could not anticipate an effect size using the existing literature. However, other intervention types with a population at high risk for violent offending have used violence outcomes and randomised designs. The most promising intervention in the YEF Toolkit [19] is Cognitive Behavioural Therapy. CBT interventions are associated with a 25% reduction relative to controls [20]. Using this statistic as a guide, we proposed that effects of 10%, 20%, 30% and 40% relative reductions in police-recorded violence against the person would be reasonable effect sizes.

#### Simulation

Based on this information, we created 10,000 simulated data sets with a similar distribution of the outcome for each of 32 combinations of effect size and sample size (see Table 2). Effect size was simulated by artificially manipulating the outcome for the treatment group and this was modelled using a negative binomial regression analysis. For each combination of effect size and sample size, the proportion of the 10,000 estimates of treatment effect that were statistically significant was stored and is visualised in Fig 1. Reproducible code for these analyses is included as a S1 File.

**Fig 1 pone.0301023.g001:**
[figure not shown]
Statistical power across three effect sizes.

**Table 2 pone.0301023.t002:** Simulated data sets.

	Relative reduction			
n	0.9	0.8	0.7	0.6
**100**	0.0154	0.042	0.2275	0.3248
**200**	0.0231	0.091	0.4958	0.6393
**300**	0.029	0.1349	0.6803	0.8371
**400**	0.0354	0.1859	0.8255	0.9391
**600**	0.0348	0.2745	0.954	0.993
**800**	0.0397	0.3447	0.99	0.999
**1700**	0.04	0.6461	1	1
**2500**	0.0417	0.8334	1	1

The graph illustrates the relative importance of effect size (‘relative change’) and sample size to statistical power. Using these simulations, we concluded that it is unlikely that five sufficiently powered trials would be achievable, even in the most optimistic of treatment effects. Consequently, as the site interventions are largely homogenous—designed according to the same framework and with comparable populations—an option to pool the data from all five sites as a multi-centred trial was considered. This pooling would achieve a sample size of approximately 1,700. Based on this sample size, a relative reduction of 26% would be detectable in 80% of trials. Therefore, pooling was determined to be the best trade-off in terms of value for money and feasibility to detect a plausible effect.

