## Discussion

This protocol outlines the process and impact evaluation methodology for the most extensive multisite evaluation of focused deterrence in the UK. Spanning five distinct sites with seven trials, the evaluation includes a cohort of approximately 2,000 individuals, marking it as the only multisite trial of focused deterrence. The protocol uses an integrated realist evaluation framework with a multi-site parallel RCT design to evaluate the efficacy of focused deterrence as an intervention for reducing violent offending among individuals aged 14 and older who are at risk of violent offending in England. To the authors’ knowledge, this will be the first multi-site impact and process evaluation of a UK-based violence reduction intervention. The anticipated findings will offer pivotal insights for formulating future violence prevention policies in the UK. They are also expected to contribute significantly to the corpus of literature on violence prevention and intervention evaluation.

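### Table 2's power figures contradict one another, so the 26% reduction stated as detectable at about 1,700 participants is not supported

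*Protocol article*

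**What the plan says.** The Statistical power section describes 10,000 simulated data sets for each of 32 combinations of effect and sample size. The effects come from the Effect size subsection: "effects of 10%, 20%, 30% and 40% relative reductions in police-recorded violence against the person would be reasonable effect sizes". The Simulation subsection says how they were imposed: "Effect size was simulated by artificially manipulating the outcome for the treatment group and this was modelled using a negative binomial regression analysis". Table 2 prints the resulting power under columns 0.9, 0.8, 0.7 and 0.6, headed as relative reductions although they are rate ratios.

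The text below Table 2 says of the five sites' data: "This pooling would achieve a sample size of approximately 1,700". It then gives the detectable effect: "Based on this sample size, a relative reduction of 26% would be detectable in 80% of trials". The Abstract (Methods) repeats it: "Based on this pooled sample size, a relative reduction of 26% would be detectable in 80% of trials".

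The article does not state the mean or dispersion of the negative binomial, the alpha or sidedness of the test, or whether n in Table 2 is a total or a per-arm number. The code is in S1, which is not shown.

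**The concern.** Power at a fixed n should rise smoothly with the log rate ratio. Table 2 does not behave this way: its 10% column never rises above 0.042, there is a very large step between 20% and 30%, and almost no step from 30% to 40%. The detectable effect of 26% is not one of the simulated columns and does not follow from the row for 1,700.

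The 26% is the only detectable effect that the article states. It stands in the abstract, it supports the argument for pooling, and it sits next to the 25% reduction for cognitive behavioural therapy used as a benchmark. A reader of Table 2 would conclude that a 10% reduction cannot be found at any of the sizes considered and that 20% is underpowered at 1,700. Neither conclusion is safe if the table is faulty.

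**Working it through.** **Inputs.** Power values are from Table 2. Two-sided alpha of 0.05 is an assumption, suggested by the 95% confidence intervals in the analysis section. For a Wald test of the log rate ratio, λ = Φ⁻¹(power) + 1.96 and SE = |ln RR| / λ. SE scales with 1/√n. The log rate ratios are −0.1054 (0.9), −0.2231 (0.8), −0.3567 (0.7) and −0.5108 (0.6).

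**1. Trying to reproduce 26% from the 1,700 row** (0.04 / 0.6461 / 1 / 1).
- 20% cell: λ = 0.375 + 1.960 = 2.335, so SE = 0.2231 / 2.335 = 0.0956.
- Reduction with 80% power: 1 − exp(−2.802 × 0.0956) = 23.5%.
- Power at 26%: 0.3011 / 0.0956 = 3.150, and Φ(3.150 − 1.960) = 0.88.
- Linear interpolation: 20% + 10% × (0.80 − 0.6461) / (1 − 0.6461) = 24.3%.

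The 26% is not reproduced.

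**2. The 10% column.** At n=2,500 the 20% cell (0.8334) gives λ = 2.928. For 10%, λ = 2.928 × 0.1054 / 0.2231 = 1.382, so power is about 0.28 (0.18 to 0.34 for alpha from 0.01 to 0.10). Table 2 prints 0.0417. With 10,000 runs, the Monte Carlo standard error at 0.05 is √(0.05 × 0.95 / 10,000) = 0.0022. The printed value is thus (0.05 − 0.0417) / 0.0022 ≈ 3.8 standard errors below the rate expected with no effect at all.

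**3. The n=400 row.** One sample size should give nearly one SE.

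| Reduction | Printed power | λ | Implied SE | Power implied by the 30% cell |
|---|---|---|---|---|
| 10% | 0.0354 | cannot be inverted | – | 0.14 |
| 20% | 0.1859 | 1.067 | 0.209 | 0.44 |
| 30% | 0.8255 | 2.897 | 0.123 | (0.8255) |
| 40% | 0.9391 | 3.507 | 0.146 | 0.986 |

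The SE of a log rate ratio does rise a little as the treated mean falls. From 20% to 30% it can rise by at most √[(1 + 1/0.7) / (1 + 1/0.8)] = 1.04. The table needs it to fall by about 40% (0.209 to 0.123).

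**4. Detectable effect at n=1,700 from other cells**, using SE × √(n / 1,700).
- 20% column: 24.7% (n=400), 23.5% (n=1,700), 22.8% (n=2,500).
- 30% column: 15.4% (n=400), 14.8% (n=800).
- 40% column: 18.5% (n=300), 18.0% (n=400).

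Cells with n of 400 or more span about 15% to 25%. Two low-power cells in the 20% column give more (26.4% from 0.1349 at n=300, 29.0% from 0.091 at n=200), but they are long extrapolations, and the same column has a direct result at 1,700.

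**5. A candidate cause.** Suppose treated counts were multiplied by the column factor and rounded. A count of 1 stays 1 under every factor used. Under ×0.9, counts of 0 to 4 do not change. Under ×0.8, 3 is the first count to change. A 2 becomes 1 only below 0.75: 2 × 0.75 = 1.5 goes to 2 with half-to-even rounding, and 2 × 0.74 = 1.48 goes to 1. A negative binomial with rounding was fitted to all 32 cells. With n as total (mean 1.09, dispersion 2.47) the sum of squared errors is 0.019; with n per arm (mean 0.76, dispersion 0.92) it is 0.023. A smooth one-parameter curve without rounding gives 0.46. Simulation from the first fit (1,500 runs per cell):

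| n | Simulated with rounding (10 / 20 / 30 / 40%) | Table 2 |
|---|---|---|
| 400 | 0.05 / 0.195 / 0.79 / 0.93 | 0.0354 / 0.1859 / 0.8255 / 0.9391 |
| 1,700 | 0.05 / 0.67 / 1.00 / 1.00 | 0.04 / 0.6461 / 1 / 1 |

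At n=1,700 the simulated power is 0.70 at a nominal 25% and 1.00 at a nominal 26%.

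**6. The same distributions without rounding**, solving −ln RR / √[(1/μ + 1/(μ·RR) + 2/θ) / n per arm] = 2.80, where θ is the fitted dispersion. With 850 per arm: about 15% (first fit) and about 20% (second fit). With 1,700 per arm under the second fit: about 14%.

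**The case against.** Three objections have force.

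First, the rounding account is incomplete. At n=100 the fitted rounding model gives about 0.05, 0.085 and 0.28 for 10%, 20% and 30%, where Table 2 prints 0.0154, 0.042 and 0.2275. An effect rounded almost to nothing should still reject at about 5%. Under rounding, power at 26% would be near 1.00, not 0.80, so one must also suppose that 26% was reported as the first whole percentage above 80%. A reader might infer that 26% is a proven artefact and that the simulated effects were not those labelled. Without S1 the document does not show this; rounding remains an inference.

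Second, alpha and sidedness are unstated. If only significant reductions were counted at one-sided 2.5%, the floor would be 0.025 and the larger-n values in the 10% column would exceed it. That does not rescue the table. At n=2,500 it gives λ = −1.731 + 1.960 = 0.23 for 10%, against the 1.38 implied by the 20% cell. The n=400 contradiction is also untouched.

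Third, the analysis section admits that the power model differs from the analysis model and promises updated power calculations in the statistical analysis plan, once site data show the outcome distribution. This lowers the cost of the error but does not cure it. The promise does not concern how effects were generated, and the same code on new data could repeat the fault.

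Two further inferences should be resisted. The text that "the evaluation includes a cohort of approximately 2,000 individuals" does not clearly contradict 1,700, since a cohort may exceed the number required. What a null result excludes will be set by the observed confidence interval, not by prospective power.

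**Conclusion.** The concern holds for Table 2 and for the 26% derived from it. The contradiction rests on the printed figures and survives other alpha levels and either reading of n. On the article's own 1,700 row, 80% power is reached at about 23.5% (24.3% by interpolation), and power at 26% is about 0.88. Across cells with n of 400 or more, the answer ranges from about 15% to 25%.

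Scaling and rounding is the likely cause because it reproduces most cells and puts a jump between 25% and 26%, but it is unconfirmed. A reader might infer that the trial is underpowered. The figures point the other way: if rounding is the cause, the stated effect is probably too large and power is understated. Nor can one corrected value be fixed from the article. Under distributions fitted to Table 2 it would be about 14% to 20%, depending on whether n is total or per arm, and these figures assume a negative binomial analysis. The column heading is a minor labelling slip.

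**What to change.** 1. Check in the S1 code how the treated outcome was altered and which rejection rule was used.
2. Re-run the simulation with treated counts drawn from a negative binomial whose mean is multiplied by the rate ratio, or by binomial thinning of counts. Do not round scaled counts.
3. Confirm a rejection rate of about 5% at a rate ratio of 1.
4. State the mean, dispersion, alpha and sidedness, and whether n is total or per arm. Label the Table 2 columns as rate ratios.
5. Replace Table 2, Fig 1 and the 26% in both the abstract and the text, and carry the corrected generator into the power update promised for the statistical analysis plan.

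The cost is a few lines of code and restated figures. No extra participants are needed.
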